**Confidential Information**

The information contained in this protocol is confidential and is intended for the use of clinical investigators. It is the property of Eli Lilly and Company or its subsidiaries and should not be copied by or distributed to persons not involved in the clinical investigation of Atomoxetine hydrochloride (LY139603), unless such persons are bound by a confidentiality agreement with Eli Lilly and Company or

its subsidiaries.

Atomoxetine Hydrochloride (LY139603)

Study LYDZ(b) is a Phase IV, multi-center double-blind, placebo-controlled trial

of atomoxetine treatment in young adults with ADHD. Patients will be treated for

12 weeks in the double-blind phase with an option to enter a 12-week open-label extension period.

Eli Lilly and Company

Indianapolis, Indiana USA 46285

Protocol Approved by Lilly: 17 November 2006

Protocol Amendment (a) Approved by Lilly: 25 April 2007

Protocol Amendment (b) Approved by Lilly: 17 December 2008

**2. Synopsis**

**Study Rationale**

ADHD in young adulthood is associated with significant functional impairments, thus, treating young adults with ADHD may prove critically important in alleviating or lessening these. The objective of Study LYDZ(b) is to prospectively evaluate atomoxetine’s efficacy in treating ADHD symptoms and atomoxetine’s effect on functional outcomes in the young adult patient population.

**Clinical Protocol Synopsis: Study B4Z-US-LYDZ(b)**

| **Name of Investigational Product:** Atomoxetine hydrochloride (LY139603) | |
| --- | --- |
| **Title of Study:** A Double-Blind Study of Atomoxetine Hydrochloride versus Placebo for the Treatment of ADHD in Young Adults with an Assessment of Associated Functional Outcomes | |
| **Number of Planned Patients/Subjects:**  Entered: 550  Enrolled/Randomized: 446  Completed: 117 | **Phase of Development:** IV |
| **Length of Study:** 19 Months  Planned first patient visit: 16 August 2007 Planned last patient visit: 10 March 2009 | |
| **Objectives:**  **Primary Objective:** The primary objective of this study is to compare the efficacy of atomoxetine at  40-100 mg/day dosed BID and placebo on the reduction of ADHD symptoms after 12 weeks of double- blind treatment as measured by the mean change in the Conners’ Adult ADHD Rating Scale- Investigator Rated: Screening Version (CAARS-Inv:SV) total ADHD symptom score in young adults ages 18 to 30 who meet criteria for ADHD as defined by DSM-IV-TR.  **Secondary Objectives:** The secondary objectives of the study are:  • To assess the efficacy of atomoxetine therapy compared with placebo on the total score of the  Adult ADHD Quality of Life -29 (AAQOL-29).  • To assess the efficacy of atomoxetine therapy compared with placebo on the subscales of the AAQOL-29 in the following order: Relationship; Life Productivity; Psychological Health; and Life Outlook.  • To test the hypothesis that atomoxetine improves symptoms of ADHD compared to placebo after  12 weeks of treatment on the mean change from baseline to endpoint as measured by:  -Clinical Global Impression-ADHD-Severity (CGI-ADHD-S)  -CAARS Self Report (CAARS-S:SV)  -Patient Global Impression – Improvement (PGI-I)  • Montgomery Asberg Depression Rating Scale (MADRS): To assess the effect of atomoxetine in treating symptoms of depression in adults with ADHD as measured by the mean change in the total score after 12 weeks of treatment.  • Beck Anxiety Inventory (BAI): To assess the effect of atomoxetine in treating symptoms of anxiety in adults with ADHD as measured by the mean change in the total score after 12 weeks of treatment.  • To assess the correlation between the improvements on the AAQOL-29 Total Score with symptom reduction as measured by improvement on the CAARS-Inv:SV total ADHD symptom score. | |
| **Study Design:** Study B4Z-US-LYDZ(b) is a multi-center, 12-week, randomized, placebo-controlled, double-blind, trial with 3 study periods for the evaluation of safety and efficacy between atomoxetine and placebo in approximately 440 adult outpatients (age 18 to 30) with ADHD at approximately 35 sites in the United States and Puerto Rico. The protocol design contains a community sample (CS), and non- interventional health outcomes data will be collected from CS participant via web-based self-reporting done through the study website. | |
| **Diagnosis and Main Criteria for Inclusion and Exclusions:** Male or female outpatients 18 to 30 years of age meeting *Diagnostic and Statistical Manual of Mental Disorder, Fourth Edition Text Revision* (DSM-IV-TR) criteria for Attention-Deficit/Hyperactivity Disorders (ADHD) as assessed by the ADHD Clinician Diagnostic Scale (ACDS). | |

| **Test Product, Dosage and Mode of Administration:** In the double-blind phase, atomoxetine 40-  100 mg/day given as 20-, 25-, or 40-mg capsules orally, twice daily (BID). In the open-label extension period, atomoxetine 36-100 mg/day given as 18-, 40-, or 60-mg capsules orally, once daily (QD) or BID. |
| --- |
| **Planned Duration of Treatment:** Patients will be treated for 12 weeks in the double-blind phase with an option to enter a 12-week open-label extension period.  screening period (Study Period I): 5 to 28 days treatment period (Study Period II): 12 weeks  optional open-label extension period (Study Period III): 12 weeks |
| **Reference Therapy, Dose and Mode of Administration:** Placebo in capsule form given orally BID. |
| **Criteria for Evaluation:**  Primary Efficacy Measure:  Conners’ Adult ADHD Rating Scale-Investigator Rated: Screening Version (CAARS-Inv:SV) Secondary Efficacy Measures:  Adult ADHD Quality of Life (AAQOL-29)  Clinical Global Impression-ADHD-Severity (CGI-ADHD-S)  Conners’ Adult Attention-Deficit/Hyperactivity Disorder Rating Scale–Self Report: Screening Version- Administered (CAARS-S:SV)  Patient Global Impression-Improvement (PGI-I) Montgomery Asberg Depression Rating Scale (MADRS) Columbia Suicide-Severity Rating Scale:  Beck Anxiety Inventory (BAI)  Secondary Functional Outcome Measures:  Habits Timeline Followback (TLFB): Alcohol, Nicotine, Caffeine, Marijuana, and Drugs  Fagerstrom Test for Nicotine Dependence (FTND) Social Adaptation Self-Evaluation Scale (SASS) Driving Behavior Survey (Self-Report)  Driving Behavior Survey (Other-Report)  Behavior Rating Inventory of Executive Function-Adult Version (BRIEF-A) Epworth Sleepiness Scale (ESS)  Safety: Safety will be assessed by summarizing and analyzing adverse events, vital signs, weight, electrocardiograms (ECG), and concomitant medications use. |

**Statistical Methods:**

Statistical:

The primary summary measure, the CAARS-Inv:SV total ADHD symptom score as well as the Inattention subscale score, and Hyperactivity-Impulsivity subscale score, will be analyzed using a restricted maximum likelihood (REML)-based, mixed model repeated measures (MMRM) technique. The model will include the fixed, categorical effects of treatment, investigator, visit, and treatment-by-

visit interaction as well as the continuous, fixed covariates of baseline (last of scores at Visit 1 and Visit 2) score and baseline score-by-visit interaction. Secondary evidence of efficacy from the primary analysis will be based on the main effect of treatment and the treatment-by-visit interaction terms from the

MMRM analysis. This measure will be summarized separately during Study Period III. All statistical tests will be two-sided and will be conducted at the 5% significance level.

As supporting evidence, the CAARS-Inv:SV total ADHD symptom score as well as the Inattention subscale score, and Hyperactivity-Impulsivity subscale score, will be analyzed using a last observation carried forward (LOCF) analysis. Change from baseline to LOCF endpoint will be compared across treatments using an ANCOVA model with terms for baseline, treatment, and investigator.

The first gated secondary objective is to assess the efficacy of atomoxetine therapy compared with placebo on the total score of the Adult ADHD Quality of Life -29 (AAQOL-29) using a treatment contrast from the repeated measures mixed effects model at the final post baseline visit. The repeated measures model will include the same terms as that used for the primary efficacy measure. This measure will be summarized separately during Study Period III.

The next gated secondary objective is to assess the efficacy of atomoxetine therapy compared with placebo on the subscales of the AAQOL-29 in the following order: Relationship; Life Productivity; Psychological Health; and Life Outlook using a treatment contrast from the repeated measures mixed effects model at the final post baseline visit. The repeated measures model will include the same terms as that used for the primary efficacy measure. These subscale measures will be summarized separately during Study Period III.

Approximately 440 patients will be randomized in a 1:1 ratio between atomoxetine and placebo

(220 patients per group). This sample size has been selected to allow for more than 80% power at the end of the study, assuming a 68% retention rate over 12 weeks. Safety analysis will include all randomized patients who take at least one dose of study drug. The incidence of treatment-emergent adverse events (TEAE) will be summarized by the following subgroups; investigational site, prior-stimulant-use strata, ADHD subtype, gender, and age. No interim analyses are planned for this study.

**4. Abbreviations and Definitions**

**AAQOL-29** Adult ADHD Quality of Life-29

**ACDS v1.2** Adult ADHD Clinician Diagnostic Scale version 1.2

**ADHD** Attention-Deficit/Hyperactivity Disorder

**ASRS** Adult ADHD Symptom Rating Scale v1.1

**Active Treatment or Active Study Drug**

Indicates that the patient is receiving atomoxetine.

**Adverse Event (AE)** Any untoward medical occurrence in a patient or clinical investigation subject administered a pharmaceutical product and which does not necessarily have a causal relationship with this treatment. An adverse event can therefore be any unfavorable and unintended sign (including an abnormal laboratory finding), symptom, or disease temporally associated with the use of a medicinal (investigational) product, whether or not related to the medicinal (investigational) product.

**Audit** A systematic and independent examination of the trial-related activities and documents to determine whether the evaluated trial-related activities were conducted, and the data were recorded, analyzed, and accurately reported according to the protocol, applicable standard operating procedures (SOPs), good clinical practice (GCP), and the applicable regulatory requirement(s).

**Blinding/Masking** A procedure in which one or more parties to the trial are kept unaware of the treatment assignment(s). Double-blinding usually refers to the subject(s), investigator(s), monitor(s), and in some cases, select sponsor personnel being unaware of the treatment assignment(s).

**BRIEF-A** Behavior Rating Inventory of Executive Function – Adult Version

**CAARS-Inv:SV** Conners’ Adult ADHD Rating Scale-Investigator Rated: Screening Version

**CAARS-S:SV** Conners’ Adult ADHD Rating Scale-Self Report: Screening Version

**CGI-ADHD-S** Clinical Global Impression: ADHD-Severity

**Complaint** A complaint is any written, electronic, or oral communication that alleges deficiencies related to the identity, quality, purity, durability, reliability, safety

or effectiveness, or performance of a drug or drug delivery system.

**Compliance** Adherence to all the trial-related requirements, good clinical practice (GCP)

requirements, and the applicable regulatory requirements.

**CS** Community Sample – The community sample is a superset of subjects (who do not qualify or qualify but choose not to participate in the randomized research clinical trial (RCT) or cannot participate because an investigator site is not within their geography) from which we will obtain non-interventional health outcomes data via web-based self-reporting.

**DSM-IV™-TR** Diagnostic and Statistical Manual of Mental Disorders, Fourth Edition- Text

Revision

**ECG** Electrocardiogram

**ESS** Epworth Sleepiness Scale

**eCRF** Electronic case report form (sometimes referred to as an electronic clinical report form). An electronic form for recording study participants’ data during a clinical study, as required by the protocol.

**End of Study (Trial)** The end of the study is defined as the last visit of the last patient.

**Enroll** See Study Entry Terms

**Enter** See Study Entry Terms

**ePRO** Electronic Patient Reported Outcomes: Patient- or observer-rated scales that are collected via an electronic data capture system.

**FTND** Fagerstrom Test for Nicotine Dependence

**Full Analysis Set**

**(FAS)**

The set of patients that is as close as possible to the ideal implied by the intention-to-treat principle (all randomized patients identified by assigned treatment group, even if they deviate from the protocol or course of treatment).

**Interim Analysis** Any analysis intended to compare treatment groups at any time prior to the formal completion of a trial.

**Intention to Treat**

**(ITT)**

The principle that asserts that the effect of a treatment policy can be best assessed by evaluating on the basis of the intention to treat a subject (that is, the planned treatment regimen) rather than the actual treatment given. It has the consequence that subjects allocated to a treatment group should be followed up, assessed and analyzed as members of that group irrespective of their

compliance to the planned course of treatment.

**Investigator** A person responsible for the conduct of the clinical trial at a trial site. If a trial is conducted by a team of individuals at a trial site, the investigator is the responsible leader of the team and may be called the principal investigator.

**IRB/ERB** Institutional review board/ethical review board: A board or committee (institutional, regional, or national) composed of medical professional and non- medical members whose responsibility is to verify that the safety, welfare, and human rights of the subjects participating in a clinical trial are protected.

**MADRS** Montgomery-Asberg Depression Rating Scale

**MDD** Major depressive disorder

**Patient** A subject with a defined disease.

Those individuals participating in the Research Clinical Trial will be referred to as patients.

**PGI-I** Patient Global Impression - Improvement

**PHQ-9** Patient Health Questionnaire

**RCT** Research Clinical Trial

**SASS** Social Adaptation Self-Evaluation Scale

**SAE** Serious Adverse Event

**SCID-RV** Structured Clinical Interview for DSM-IV™-TR Axis I Disorders- Research

Version

**Study Entry Terms** Screen

The act of determining if an individual meets minimum requirements to become part of a pool of potential candidates for participation in a clinical trial. In this study, pre-screening occurs via questions answered on a study website. Eligible patients may then be further screened (for example, diagnostic psychological tests, blood draws) at the investigator site level. A privacy statement and/or informed consent is obtained prior to individuals answering any questions to determine eligibility for the trial.

Enter/Enrolled

Entered patients are those patients who meet pre-screening requirements (from the web-based screening phase) and are deemed eligible to proceed with further evaluation to determine eligibility for the Research Clinical Trial at an investigator site. Entered patients will have at least a Visit 1 recorded.

Enrolled patients are those patients who meet all of the inclusion criteria and none of the exclusion criteria, agree to continue participation in the study, and complete the Visit 2. These patients are considered as “enrolled in the study” and will receive study medication at the end of Visit 2.

**Subject** An individual who is or becomes a participant in clinical research, either as a recipient of the test article or as a control. A subject may be either a healthy human or a patient.

Those individuals participating in screening and those who are in the

Community Sample of the trial will be referred to as subjects.

**TLFB** Habits Timeline Followback (TLFB): Alcohol, Nicotine, Caffeine, Marijuana, and Drugs

**Treatment- Emergent Adverse Event (TEAE)**

Any untoward medical occurrence that either occurs or worsens at any time after treatment baseline and which does not necessarily have to have a causal relationship with this treatment (also called treatment-emergent signs and symptoms [TESS]).

**A Double-Blind Study of Atomoxetine Hydrochloride versus Placebo for the Treatment of ADHD in Young Adults with an Assessment of Associated Functional Outcomes**

**5. Introduction**

Atomoxetine hydrochloride1 (hereafter referred to as atomoxetine), a potent and highly selective inhibitor of the presynaptic norepinephrine transporter, is approved by the FDA as a treatment for Attention-Deficit/Hyperactivity Disorder (ADHD) in children, adolescents, and adults, as defined by the Diagnostic and Statistical Manual of Mental Disorders, Fourth Edition-Text Revision (DSM-IV-TR™); (APA [American Psychiatric Association] 2000). Atomoxetine was approved for use in adults with ADHD based on two pivotal trials: B4Z-US-LYAA and B4Z-US-LYAO (Michelson et al. 2003).

ADHD in young adulthood can create life-long devastating functional outcomes, thus, treating young adults with ADHD is critically important. Sixty percent of children and adolescents who have ADHD continue to have symptoms of ADHD into adulthood (Hechtman 1992; Barkley 1998). Impairment due to ADHD can have potentially long- lasting negative effects in young adults as they transition into adulthood. Decisions made by young adults as they move away from home, go to college, and start careers affect the trajectories of their lives and can having sustaining impact. Furthermore, as children and adolescents with ADHD transition into adulthood, they are more likely to develop comorbid psychopathology and engage in high risk behaviors than their non-ADHD counterparts (Biederman et al. 2006). In a 10-year prospective study in male youths with ADHD, subjects reported higher rates of anti-social, addictive, mood, and anxiety disorders compared to control subjects (Biederman et al. 2006). If left untreated, ADHD impairment puts this patient population at greater risk for negative life-long

consequences. For example, young adults with ADHD are more likely to have problems

sustaining long-term intimate relationships and twice as likely to be divorced or separated

(Biederman et al. 1993). Further, studies of driving behaviors in young adults with ADHD showed greater risks of speeding, traffic violation citations, and a tendency for more auto crashes than counterparts without ADHD. (Barkley et al. 1996). Additionally, the propensity for addictive behaviors is greater in adults with ADHD in that they are more likely to be smokers and are more likely to have alcohol and substance abuse comorbidities (Biederman et al. 1993; Pomerleau et al. 1995).

1 Atomoxetine or atomoxetine hydrochloride was formerly known as tomoxetine or tomoxetine hydrochloride. In agreement with the USAN Council (United States Adopted Names Council), the generic name was changed to minimize the possibility of confusion with tomoxifen, which is often used in the treatment for breast cancer.

The treatment of ADHD in the young adult is critical. Many therapies besides atomoxetine pose potential risks that are heightened in this particular demographic population. Therapies currently available for the treatment of ADHD, other than atomoxetine, include prescription stimulants such as methylphenidates, dextroamphetamine, and mixed amphetamines salts. However, these types of medications carry a risk for abuse and diversion (sell, trade, or give away), particularly for college-aged students and young adults. Varying reports of non-medical use of methylphenidates among college students suggests a lifetime use ranging from 3% to

16% and use within the past year of 5.7% (McCabe et al. 2005). Further, a study

sponsored by Eli Lilly reported lifetime non-medical use of long-acting stimulants (approximately 2.1%) (Novak et al. 2006). When examining the rate of diversion of prescribed stimulants among undergraduate students prescribed stimulants, 54% reported being approached to divert their medication (McCabe et al. 2006).

Atomoxetine is not subject to the problems of diversion and abuse associated with stimulants. Furthermore, atomoxetine may offer a treatment for ADHD and its negative functional outcomes in this specific population that is particularly effective. To date, this potential effectiveness has only been explored retrospectively. The question of which patients will most likely respond to a trial of atomoxetine is one that is very pertinent to prescribers. Many physicians believe that atomoxetine response is, in general, less robust than they would expect from some other alternative stimulant medications for ADHD. However, post hoc analyses of previous Lilly trials (B4Z-US-LYBV, B4Z-MC-LYAA, B4Z-MC-LYAO, and B4Z-US-LYCU) suggest that young adults respond robustly to atomoxetine. There is evidence to suggest that young adults may represent a

demographic group whose response to atomoxetine is more robust than physicians

typically expect; however, these findings have been replicated only in a post hoc fashion and have not been confirmed in a prospective trial. The objective of Study LYDZ(b) is to prospectively evaluate atomoxetine’s efficacy in treating ADHD symptoms and atomoxetine’s effect on functional outcomes in the young adult patient population.

In addition to the aims of the randomized clinical trial portion of Study LYDZ(b) discussed earlier, this study incorporates a community sample which is a superset of subjects who do not qualify or qualify but choose not to participate in the randomized research clinical trial (RCT) or qualify but cannot participate because an investigator site is not within their geography. From this superset of subjects, we will obtain non-

interventional health outcomes data via web-based self reporting to assess the

associations between ADHD symptom complexity and severity on functional outcomes for young adults with ADHD in this community sample. Results from the community sample will be reported separately from the main protocol study report. The Protocol Attachment LYDZ(b).5 further describes the community sample.

More detailed information about the known benefits and risks of atomoxetine hydrochloride may be found in the Investigator's Brochure (IB).

**6. Objectives**

**6.1. Primary Objective**

The primary objective is to compare the efficacy of atomoxetine at 40 - 100 mg/day dosed BID and placebo on the reduction of ADHD symptoms after 12 weeks of double- blind treatment as measured by the mean change in the Conners’ Adult ADHD Rating Scale- Investigator Rated: Screening Version (CAARS-Inv:SV) total ADHD symptom score in young adults ages 18 to 30 who meet criteria for ADHD as defined by DSM-IV- TR.

**6.2. Secondary Objectives**

***6.2.1. Gated Secondary Objectives***

The following two secondary objectives will be tested using the Gatekeeper strategy (Westfall 2001). Atomoxetine and placebo will be compared in a stepwise fashion in order as indicated below. Testing will stop when a measure fails to show statistical significance favoring atomoxetine (p<0.05) based on a 2-sided test of significance.

• To assess the efficacy of atomoxetine therapy compared with placebo on the total score of the Adult ADHD Quality of Life -29 (AAQOL-29).

• To assess the efficacy of atomoxetine therapy compared with placebo on the subscales of the AAQOL-29 in the following order: Relationship; Life Productivity; Psychological Health; and Life Outlook.

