**12.2. Statistical and Analytical Plans**

***12.2.1. General Considerations***

Statistical analysis of this study will be the responsibility of Eli Lilly and Company or an approved vendor of Eli Lilly and Company.

Treatment effects for all efficacy and safety variables will be evaluated based on a two- sided significance level of 0.05, and the interaction effects at 0.10. Any change to the data analysis methods described in the protocol will require an amendment ONLY if it changes a principal feature of the protocol. Any other changes in the data analysis methods described in this protocol will be documented in the Statistical Analysis Plan (SAP) prior to unblinding of the data. Such changes will not require protocol amendments. If changes to the data analysis methods described in the protocol are deemed necessary the justification for making such changes will be described in the clinical study report. Additional exploratory analyses of the data will be conducted as deemed appropriate.

Active treatment phase refers to the visit interval after randomization in which the placebo lead-in period is excluded. In all the analyses, baseline will be the latest non- missing observation across all the visits in the screening phase and the placebo lead-in period, before the active study drug begins. Endpoint will be the latest non-missing observation across all the post-baseline visits before.

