**12.2.1.2. Adjustment for Multiplicity**

All tests of significance in this study will be conducted at a 2-sided alpha level of 0.05, unless otherwise stated. The primary efficacy analysis will be performed on the original scale data. All other analyses will also be performed on the original scale data. No adjustments for multiple comparisons will be made. All tests of hypotheses will be considered statistically significant if the two-sided p-value is less than 0.05. No adjustments for secondary comparisons are needed since we are using a gatekeeper strategy to prevent multiplicity in the comparisons that are of the greatest interest.

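### The AAQOL-29 testing sequence is not tied to the primary result, yet it is used to justify calling every ungated test significant at 0.05

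*Protocol*

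**What the plan says.** Protocol section 6.2.1 states: "The following two secondary objectives will be tested using the Gatekeeper strategy". It continues: "Atomoxetine and placebo will be compared in a stepwise fashion in order as indicated below", and "Testing will stop when a measure fails to show statistical significance favoring atomoxetine (p<0.05) based on a 2-sided test of significance". The order is AAQOL-29 total, Relationship, Life Productivity, Psychological Health, Life Outlook. Section 12.2.8 repeats this order and calls the AAQOL-29 total the first gated secondary objective.

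Section 12.2.6 defines the primary comparison as the MMRM treatment contrast at Visit 6, tested two-sided at 5%. It does not mention the gate.

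Section 12.2.1.2 makes three statements: "No adjustments for multiple comparisons will be made"; "All tests of hypotheses will be considered statistically significant if the two-sided p-value is less than 0.05"; and "No adjustments for secondary comparisons are needed since we are using a gatekeeper strategy to prevent multiplicity". The last sentence goes on to limit the purpose of the gate: "we are using a gatekeeper strategy to prevent multiplicity in the comparisons that are of the greatest interest".

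Outside the gate, sections 6.2.2 and 6.2.3 list further treatment comparisons. Table LYDZ(b).3, item 2.a, includes the AAQOL-29 total and subscores again as LOCF change. Section 12.2.8.1 analyses items 2.a to 2.n by ANCOVA.

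On interactions, section 12.2.1 sets a two-"sided significance level of 0.05, and the interaction effects at 0.10", while section 12.2.6 puts all its tests at 5% and names the treatment-by-visit interaction as secondary evidence of efficacy.

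**The concern.** A gatekeeping procedure protects the study-wise error rate only if the primary test is its first step. Here the stopping rule covers five AAQOL-29 tests and the primary stands beside them. If the primary fails, no written rule prevents a claim on quality of life.

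Section 12.2.1.2 then extends the benefit of the gate to tests that it does not cover. The additional secondary and functional outcomes are declared significant at an unadjusted 0.05 on the ground that a gatekeeper is in use, although none of them is in it.

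Finally, the gated family can be bypassed. An AAQOL-29 score that fails in the sequence, or is never reached, is tested again by LOCF ANCOVA and may be called significant there.

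At stake is which claims the study report may make, above all after a failed primary.

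**Working it through.** **The plan's own figure.** The protocol states no family-wise error rate. The nearest figure is the power for the first gated test in section 12.1. With 220 per arm and 68% completing, n = 220 × 0.68 = 149.6 per arm, and power ≈ Φ(d × √(n/2) − 1.96), where √(149.6/2) = 8.649.

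- d = 0.325: Φ(2.811 − 1.96) = 80.3% (stated 80%)
- d = 0.35: Φ(3.027 − 1.96) = 85.7% (stated 85%)
- d = 0.40: Φ(3.459 − 1.96) = 93.3% (stated 93%)

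The figures reproduce. They are the power of a stand-alone two-sided 5% test, with no condition on the primary.

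**Inputs for the error rates.** Two-sided 0.05 per test (12.2.1.2); five gated tests in fixed order (6.2.1); one primary contrast (12.2.6). There are 16 ungated treatment comparisons, counting total scores only:

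- Five in 6.2.2: CGI-ADHD-S, CAARS-S:SV, PGI-I, MADRS, BAI.
- Eleven in 6.2.3: five Timeline Followback habits, FTND, SASS, two driving surveys, BRIEF-A, Epworth.

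The documents give no correlations between outcomes. The values below are assumptions, with the same correlation between every pair, all nulls true, and 400,000 simulated draws.

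**Within the gate.** A false claim requires the first true null in the order to be rejected, so error over the five tests is at most 5%.

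**Primary plus a separate gate.** Only the primary and the AAQOL-29 total need be considered when all nulls hold: 1 − 0.95² = 9.75% if independent, and at most 0.05 + 0.05 = 10% under any dependence.

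**Primary as step 1.** All six tests lie in one sequence: at most 5%.

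**Ungated tests.** 1 − 0.95¹⁶ = 56% if independent; expected number of false positives 16 × 0.05 = 0.8. For the five AAQOL-29 scores retested by LOCF ANCOVA, 1 − 0.95⁵ = 23% if independent.

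| Assumed correlation | Primary and gate unlinked | Primary as step 1 | 16 ungated tests | 5 LOCF AAQOL-29 tests |
|---|---|---|---|---|
| 0 | 9.75% | 5.0% | 56% | 23% |
| 0.3 | 9.5% | 5.0% | 47% | 21% |
| 0.5 | 9.1% | 5.0% | 37% | 18% |
| 0.7 | 8.4% | 5.0% | 26% | 15% |
| 0.9 | 7.0% | 5.0% | 15% | 10% |

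These count false positives in either direction. Counting only false claims in favour of atomoxetine, the independent figures are 1 − 0.975² = 4.9% against a target of 2.5%, and 1 − 0.975¹⁶ = 33% for the 16 tests.

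**The case against.** The strongest reply is that the primary was obviously meant to be the gate. The section heading speaks of gated secondary objectives, the method is called gatekeeping, and the title of the cited source concerns primary and secondary endpoints. No sentence says that the AAQOL-29 will be tested after a failed primary. This stands as a reading of intent, and a reader who inferred that the protocol authorises such a claim would go too far. It does not supply the missing rule, since the protocol spells out every other step, down to the order of the subscales.

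A reader might also infer that there is no error control at all. That is wrong. The sequence holds 5% within its five tests, the primary is a single 5% contrast, and section 12.2.1.2 claims protection only for the comparisons of greatest interest. What remains faulty is the opening of that sentence, which dispenses with adjustment for secondary comparisons in general.

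A larger count is tempting. Adding responder, remitter, time-to-event, smoking, CAARS subscale, main-effect and interaction tests gives about 28, and 1 − 0.95²⁸ = 76%. That figure should not be used, because many of these tests share data: responders and remitters are cut-points of scales already tested, the two CAARS subscales sum to the primary score, and the main effect and interaction come from the primary model.

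The two alpha levels for interactions are a minor ambiguity. The only specific use of 0.10 is the site interaction in section 12.2.10, and the specific 5% rule in 12.2.6 can reasonably govern the MMRM.

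Testing additional secondaries at an unadjusted 0.05 is common practice. The objection here is to calling them significant and citing the gate as the reason.

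**Conclusion.** The point holds in a limited form, with three parts.

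- The sequence controls error at 5% among the five AAQOL-29 tests but is not written as conditional on the primary. The literal rule gives 9.75% under independence, about 9.1% at an assumed correlation of 0.5, and never more than 10%.
- Section 12.2.1.2 wrongly relies on the gate to label ungated tests significant. For the 16 comparisons in 6.2.2 and 6.2.3, the chance of at least one false positive is 56% under independence and about 37% at correlation 0.5. Both figures assume that every null is true.
- The LOCF ANCOVA in Table LYDZ(b).3, item 2.a, lets an AAQOL-29 score that failed or was not reached in the gate be called significant.

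The primary test itself, its alpha and the sample size are unaffected. The matter goes beyond omitted detail, because section 12.2.1.2 states a positive rule. It should be settled before unblinding.

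**What to change.** In sections 6.2.1 and 12.2.1.2, write one sequence: step 1, the primary CAARS-Inv:SV total MMRM contrast at Visit 6, significant in favour of atomoxetine; step 2, the AAQOL-29 total; steps 3 to 6, the four subscales in the order already given. Each step is tested at two-sided 0.05, and testing stops at the first failure.

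In section 12.2.1.2, replace the sentence that declares every p-value below 0.05 significant, and the one that dispenses with adjustment for secondary comparisons. The new text should say that only tests in this sequence may be called statistically significant. All others are supportive with nominal p-values, including the LOCF AAQOL-29 tests, the CAARS subscales, the treatment main effect and the treatment-by-visit interaction. The statement "No adjustments for multiple comparisons will be made" may stay if it is made clear that it refers to the alpha at each step.

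In section 12.2.1, say that the 0.10 level applies to subgroup interactions only.

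The cost is a few sentences, with no change to sample size, per-test alpha or conduct. Some secondary results can no longer be called significant. An AAQOL-29 claim will also require a successful primary. With the stated 90% power for the primary and 80% for the AAQOL-29 total at effect size 0.325, the chance of passing both is 0.90 × 0.80 = 72% if independent, and at most 80%. If the primary was always meant to open the gate, this cost was already implied.
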